# Protocol for a cluster-randomised non-inferiority trial of one versus two doses of ivermectin for the control of scabies using a mass drug administration strategy (the RISE study)

**DOI:** 10.1136/bmjopen-2020-037305

**Published:** 2020-08-30

**Keywords:** tropical medicine, infectious diseases, dermatology, international health services

## Abstract

**Introduction:**

Scabies is a significant contributor to global morbidity, affecting approximately 200 million people at any time. Scabies is endemic in many resource-limited tropical settings. Bacterial skin infection (impetigo) frequently complicates scabies infestation in these settings. Community-wide ivermectin-based mass drug administration (MDA) is an effective control strategy for scabies in island settings, with a single round of MDA reducing population prevalence by around 90%. However, current two-dose regimens present a number of barriers to programmatic MDA implementation. We designed the Regimens of Ivermectin for Scabies Elimination (RISE) trial to investigate whether one-dose MDA may be as effective as two-dose MDA in controlling scabies in high-prevalence settings.

**Methods and analysis:**

RISE is a cluster-randomised non-inferiority trial. The study will be conducted in 20 isolated villages in Western Province of Solomon Islands where population prevalence of scabies is approximately 20%. Villages will be randomly allocated to receive either one dose or two doses of ivermectin-based MDA in a 1:1 ratio. The primary objective of the study is to determine if ivermectin-based MDA with one dose is as effective as MDA with two doses in reducing the prevalence of scabies after 12 months. Secondary objectives include the effect of ivermectin-based MDA on impetigo prevalence after 12 and 24 months, the prevalence of scabies at 24 months after the intervention, the impact on presentation to health facilities with scabies and impetigo, and the safety of one-dose and two-dose MDA.

**Ethics and dissemination:**

This trial has been approved by the ethics review committees of the Solomon Islands and the Royal Children's Hospital, Australia. Results will be disseminated in peer-reviewed publications and in meetings with the Solomon Islands Ministry of Health and Medical Services and participating communities.

**Trial registration details:**

Australian New Zealand Clinical Trials Registry: ACTRN12618001086257. Date registered: 28 June 2018.

Strengths and limitations of this studyThe cluster-randomised study design follows the implementation of the intervention at a village levelFollow-up at both 12 and 24 months will demonstrate longer term effects of the interventionThe sample size (5000 people across 20 villages) achieves a statistical power of 80%This study is being conducted in partnership with the Solomon Islands Ministry of Health and Medical Service in a culturally sensitive manner and will build the capacity of local nursing staffScabies prevalence is high in the isolated island villages where this study will be conducted (approximately 20%), therefore results may not be transferable to lower prevalence or urban settings

## Background

Scabies is a neglected tropical disease (NTD) caused by infestation with the mite *Sarcoptes scabiei* var. *hominis*. Scabies is a significant contributor to global morbidity, estimated to cause 455 million annual incident cases.^1 2^ Transmission occurs primarily as a result of skin-to-skin contact (and rarely due to fomites) and is more common in overcrowded settings, including in many tropical environments where crowding and poverty are prevalent and access to treatment limited.^3 4^ The burden of disease is substantial in many Pacific Island Countries where scabies affects one in five people and up to one in two children.^5^

Scabies infestation causes intense itch and discomfort. Furthermore, it is responsible for a considerable proportion of bacterial skin infection (impetigo) in many resource-limited settings.^6–8^ Scabies causes a breach in the skin barrier from scabetic lesions and subsequent scratching, creating an entry point for bacteria, including *Staphylococcus aureus* and *Streptococcus pyogenes*. Resulting impetigo can in turn cause severe infection and immune-mediated disease, including sepsis, glomerulonephritis and possibly rheumatic fever.^9–12^

Treatment guidelines for scabies recommend treatment of the infected individual as well as household contacts.^13 14^ Most guidelines recommend treatment with topical acaracides such as permethrin or benzoyl benzoate.^13 14^ These medications are effective, if applied to all affected areas for the correct duration, but re-infestation frequently occurs in highly endemic settings where individuals may be exposed to infected household or community members, many of whom may be asymptomatic.^15^ Therefore, attention has shifted to simultaneous treatment of whole communities, including those without symptoms of infestation, to reduce prevalence and the rate of transmission.^16^ This strategy of mass drug administration (MDA) has been used to successfully control a number of NTDs, including onchocerciasis, lymphatic filariasis (LF), trachoma and soil-transmitted helminths, and there is a growing body of evidence to support MDA for scabies control.^17–22^

Ivermectin is an antiparasitic drug in the avermectin class that is active against the scabies mite. Ivermectin-based MDA for scabies involves offering ivermectin treatment to the whole community, with the exception of young children, pregnant women and others with a contraindication to ivermectin. Permethrin cream is offered as an alternative to ivermectin for these groups. Several studies in Pacific Island Countries with high-prevalence have shown ivermectin-based MDA can reduce the population prevalence of scabies by around 90%.^7 17 23^ The Skin Health Intervention Fiji Trial (SHIFT) study in Fiji was the first comparative study to demonstrate the effectiveness of ivermectin MDA for scabies control, finding a reduction in the population prevalence of scabies from 32% at baseline to less than 2% at 12 months.^21^ These trials have all used an MDA strategy involving two doses of medication, given 7 to 14 days apart (either to the whole community or those with clinical signs of scabies).^7 23^ This is consistent with clinical recommendations for treatment of individuals.^13^ Ivermectin is known to lack ovicidal activity, therefore the second dose aims to kill newly hatched mites.^24^

In 2017, the WHO recognised scabies as a NTD, and identified the need for public health action to control scabies in endemic settings.^9^ The Strategic and Technical Advisory Group on Neglected Tropical Diseases called for further research into control strategies for scabies and the development of guidelines for the public health use of avermectins.^25^

While ivermectin-based MDA shows great promise as a control strategy for scabies, the requirement for two doses of medication at each MDA round presents barriers to implementation. Drug and implementation costs are doubled compared with single-dose MDA. Distribution is more complex and integration with programmes for other NTDs is difficult. These challenges are amplified in remote island settings where the population is dispersed across difficult to reach villages and funding for programmes is limited. These hurdles may be prohibitive to widespread implementation of scabies control, particularly in low-income settings. Therefore, the optimum dosing strategy for MDA remains an important knowledge gap.^9^ For this reason, we designed the Regimens of Ivermectin for Scabies Elimination (RISE) trial.

## Methods and analysis

### Study design

The RISE trial is a prospective, open-label comparison of one dose versus two doses of ivermectin-based MDA for the population-level control of scabies (table 1). Using a cluster-randomised design, 20 villages will be randomised to one of two intervention groups in a 1:1 ratio. Randomisation will occur at the village level, rather than the individual level, as the objective is to determine the dosing regimen for controlling scabies within whole communities. Randomisation minimises the possibility of the anticipated difference in the outcome between each group being confounded. A two-dose regimen is an appropriate comparator (rather than no-treatment or placebo) as two-doses of ivermectin-based MDA is the currently accepted dosing regimen. We chose a non-inferiority design because it is unlikely that a one-dose regimen would be superior in effectiveness to a two-dose regimen.

**Table 1 T1:** Key features of the RISE trial

Primary objective	To determine if ivermectin-based MDA with one dose is non-inferior to two-doses in reducing prevalence of scabies at 12 months
Secondary objectives	Impact of one versus two dose ivermectin-based MDA on: Population prevalence of scabies at 24 months Population prevalence of impetigo at 12 and 24 months Number of presentations to health clinics with scabies and impetigo Number of adverse events measured by passive surveillance in the 12-month period following MDA
Design	Prospective, open-label comparison using a cluster-randomised design
Sample size	20 villages (approximately 5000 participants), randomised in a 1:1 ratio to each intervention group
Intervention	Group 1: one dose of ivermectin-based MDA Group 2: two doses of ivermectin-based MDA given 7 to 14 days apart
Study setting	Western Province, Solomon Islands (scabies prevalence approximately 20%)
Inclusion criteria	All residents in the study villages
Exclusion criteria	Participants who meet exclusion criteria will not receive treatment but will still be eligible to enrol in the study and undergo skin examination Exclusion criteria are: allergy to ivermectin or permethrin; treatment within the last 7 days with ivermectin or permethrin; participant declines treatment If ivermectin is contraindicated, topical permethrin will be offered. Contraindications for ivermectin include: pregnancy; breastfeeding an infant less than 7 days old; age less than 2 years; height less than 90 cm; concurrent medication that may interact with ivermectin (for example, warfarin); or severe, acute or chronic illness on the day of MDA
Outcome measures	Presence of scabies and impetigo measured by clinical examination Conducted by trained nurses and assessed using the 2020 International Alliance for the Control of Scabies criteria Assessments will be conducted at baseline, 12 and 24 months

MDA, mass drug administration; RISE, Regimens of Ivermectin for Scabies Elimination.

However, the logistic and pragmatic advantages of a one-dose regimen compared with a two-dose regimen make a non-inferior study appealing.

The prevalence of scabies and impetigo will be measured before the intervention (baseline), and repeated at 12 and 24 months after the intervention. To measure a secondary outcome, the standard Solomon Islands Ministry of Health and Medical Services (MHMS) health facility reporting processes will be used to capture the number of presentations to health facilities with scabies and impetigo in the study catchment area for the 12-month period before the intervention and for the 24-month period after the intervention.

### Aims

The primary objective of this study is to determine if ivermectin-based MDA with one dose is non-inferior to two doses in reducing the prevalence of scabies 12 months after the intervention. The secondary objectives are to assess the impact of ivermectin-based MDA on: population prevalence of scabies after 24 months; population prevalence of impetigo after 12 and 24 months; the number of presentations to health clinics with scabies and impetigo before and after the intervention; the number of adverse events measured by passive surveillance in the 12 months after MDA in each study group. The trial will also be measuring outcomes related to the impact of ivermectin MDA on the prevalence and intensity of soil-transmitted helminths; however, this paper focusses on scabies and impetigo outcomes.

### Rationale

This study uses ivermectin-based MDA because the SHIFT trial in Fiji demonstrated the greatest reduction in scabies prevalence after ivermectin-based MDA.^21^ Ivermectin is currently the only oral therapy available for scabies and it allows greater compliance than with topical therapy. Oral therapy can be directly observed, ensuring adherence to treatment. Although ivermectin only kills the mature scabies mite and not the eggs, a single dose of treatment simultaneously administered to a whole village may reduce transmission sufficiently to reduce population prevalence. A recent Cochrane review did not find a difference in efficacy of one dose of oral ivermectin compared with two doses of oral ivermectin, but confidence in the effect estimates was low-to-moderate, with poor reporting being a major limitation.^26^ A retrospective study in Zanzibar of six rounds of annual single-dose ivermectin MDA for LF showed a 68% to 98% decline in clinical presentations and treatments for scabies, suggesting a one-dose strategy may significantly reduce transmission.^27^ By contrast, annual ivermectin MDA for LF did not reduce the prevalence of scabies in Tanzania where the baseline prevalence was less than 5%.^28^

### Study setting and participants

The study will be conducted in Western Province of Solomon Islands (figures 1 and 2). Solomon Islands is a nation in the South Pacific with a population of over 650 000 spread across 900 islands, a geography that presents many challenges for health service delivery.^29^ Solomon Islands is classified as a least developed country. It is ranked 152 out of 189 on the Human Development Index.^30^ The majority of the population depend on subsistence agriculture in rural locations. We chose Western Province for this study for several reasons: first, there is a high burden of scabies—a 2014 survey estimated an all-age scabies prevalence of 19.2%^6^; second, we expect that there will be relatively little mixing between villages because of the island geography of isolated villages with no road transport; third, there are many villages of appropriate population size (between 180 and 300) for the cluster-randomised design.

**Figure 1 F1:**
[figure not shown]
Study location in Solomon Islands.

**Figure 2 F2:**
[figure not shown]
Study location in Western Province, Solomon Islands.

Twenty villages will be selected after close consultation with the MHMS. Criteria for selecting the villages include a population of between 180 and 300 people, geographic isolation and willingness to participate in the study. All residents of the 20 selected villages will be eligible to participate. If a resident of a two-dose village does not take the first dose of medication, they will still be eligible to take a dose when the team returns to the village for the second dose.

This is a community-based study, with analysis conducted at the village level, and therefore, all residents are eligible to participate in the follow-up assessment at 12 and 24 months, regardless of whether they received treatment at baseline. Written informed consent will be obtained from all participants. Participants under the age 18 years will require written consent to be provided by a parent or guardian. Consent will be obtained at each study time point (baseline, 12 months and 24 months) (online supplementary file 1).

10.1136/bmjopen-2020-037305.supp1Supplementary data

### Inclusion and exclusion criteria

#### Inclusion criteria

All participants who provide consent are eligible to participate. If exclusion criteria for treatment are met, then consented participants are still eligible to have their skin examined.

#### Exclusion criteria

Participants who meet any of the following criteria will not receive treatment, but will be eligible to enrol in the study and undergo skin examination: allergy to ivermectin or permethrin; treatment within the last 7 days with ivermectin or permethrin; or declines treatment.

If ivermectin is contraindicated, then topical permethrin will be offered. The contraindications for ivermectin are: pregnancy; breastfeeding an infant less than 7 days old; age less than 2 years; height less than 90 cm; concurrent medication that may interact with ivermectin (eg, warfarin); or severe acute or chronic illness on the day of MDA.

### Patient and public involvement statement

The trial was designed in close consultation with stakeholders at the Solomon Islands MHMS to ensure it was culturally appropriate for the local setting. Staff from the Solomon Islands MHMS contributed to study design and identification of study sites. The study team will comprise a majority of Solomon Islander staff from Western Province. Staff are able to communicate in the local regional languages.

A team of health promotion officers from the Solomon Islands MHMS will conduct community awareness in each village, approximately 1 month prior to MDA. An illustrated information leaflet outlining the study design as well as information about scabies and the treatments will be provided during community visits. A participant information statement that contains contact details for the principal investigator and local investigator will be made available to all village residents. Community awareness and the informed consent process will be conducted in Solomon Islands Pijin and study staff who speak the local regional language will be available to provide further information or clarification as required. Results of the study will be communicated to community leaders and members by the study team.

### Intervention

Oral ivermectin will be offered to all participants, unless there is a contraindication to ivermectin. A dose of 200 µg/kg of ivermectin is recommended for the treatment of individuals with scabies.^13 31^ We will aim to dose ivermectin within a range of 150 to 250 µg/kg, as this dose has been effective in previous trials.^21^ We will use 6 mg scored tablets. Doses will be rounded to the nearest 3 mg. The tablets will be accurately halved on the score line using a pill cutter as required. As weight scales are generally unsuitable for implementation of MDA, we will use dosing strategies appropriate for larger scale programmatic roll-out.

We will use height-based dosing for children aged less than 15 years, with doses ranging from 3 mg to 12 mg, as is standard for MDA for onchocerciasis and LF.^32 33^ Adults will receive a standard dose of 12 mg, with doses adjusted based on visual assessment of body shape (9 mg for adults assessed to be malnourished and 15 mg for adults assessed to be obese). Drug distribution staff will make these assessments based on a series of body shape silhouettes.^34^ Dosing of medications for MDA based on physical appearance has been shown to be accurate and safe.^33^ Staff will undergo training and validation for these dosing techniques. Ivermectin will be administered by trained study staff who will directly observe swallowing of the tablets.

Topical permethrin 5% cream will be given to participants meeting exclusion criteria for ivermectin. Permethrin will be dosed according to clinical guidelines.^35^ Participants or carers will be counselled to apply the cream to the whole body from the neck down (in infants cream should also be applied to the scalp) and to leave it for 8 to 14 hours, or 4 hours in infants less than 2 months of age.

### Outcome measures

All participants will undergo assessment for symptoms and signs of scabies, impetigo and other skin disease.^36^ Assessment will include history questions regarding the presence of itch, contact history and a simplified skin examination. Skin examination will be limited to areas that are usually exposed (arms from above elbow to fingers, legs from above knee to toes, and head and neck). Other areas (including breasts, groin or genitals) will not be examined. Data suggest that, in this setting, a limited examination detects more than 90% cases of scabies.^36^ The skin of children less than 2 years age will be examined more generally, as scabies may be more widespread in this age group.^3^

Scabies will be diagnosed according to consensus criteria established by the International Alliance for the Control of Scabies (2020 IACS criteria).^37 38^ Categorisation will be based on the identification of typical scabies lesions, typical body distribution of lesions and presence of itch and/or positive contact history. Diagnosis will therefore use levels B (Clinical Scabies) and C (Suspected Scabies) (table 2). Microscopy was not used as it is not feasible or practical for programmatic roll-out in these remote settings. Confirmation of diagnosis with dermatoscopy was not considered feasible as the specialist skills required exceeded the training of the local health workers.

**Table 2 T2:** Case definitions for scabies using the 2020 IACS Criteria^38^

Criteria category		Used in survey
**Confirmed scabies**		
	At least one of the following:	
A1	Mites, eggs or faeces on light microscopy of skin samples	No
A2	Mites, eggs or faeces visualised on an individual using a high-powered imaging device	No
A3	Mite visualised on an individual using dermoscopy	No
**Clinical scabies**		
	At least one of the following:	
B1	Scabies burrows	No
B2	Typical lesions affecting male genitalia	No
B3	Typical lesions in a typical distribution and two history features*	Yes
**Suspected scabies**		
	At least one of the following:	
C1	Typical lesions in a typical distribution and one history feature*	Yes
C2	Atypical lesions or atypical distribution and two history features*	Yes

Diagnosis can be made at one of the three levels (A, B or C). A diagnosis of clinical or suspected scabies should only be made if other differential diagnoses are considered less likely than scabies.

*History features include (i) itch and (ii) positive contact history.

IACS, International Alliance for the Control of Scabies.

Impetigo will be recorded if papular, pustular or ulcerative lesions surrounded by erythema, or with crusts, pus or bullae are seen.^7^ This approach is consistent with the diagnostic processes in previous scabies community intervention trials. Examinations will be conducted by nurses from Western Province. Nurses will receive 1 week of theoretical and practical training in the clinical assessment for scabies and impetigo, including application of the 2020 IACS criteria (online supplementary file 2).^39^ Nurses will receive additional training prior to the follow-up surveys at 12 and 24 months.

10.1136/bmjopen-2020-037305.supp2Supplementary data

Other severe skin infections such as ulcers, abscesses or suspected cases of crusted scabies will also be recorded where noted. If these, or other significant medical conditions are noted during the survey, participants will be referred off-study to the local health clinic for assessment and management.

In addition to skin examination data, we will also collect information on presentations to health facilities in the study villages. Government health facilities in Solomon Islands routinely record the details of all attendances and admissions in paper-based registers. Cases of scabies, local and serious bacterial infections, and other skin diseases are recorded. Facilities report aggregated data using a standardised form each month. Data is transferred electronically through the District Health Information System (DHIS2) to the MHMS Health Information Statistics Unit. We will use the information from DHIS2 to assess the number of presentations to health facilities with scabies and impetigo. Data collected in the 12 months prior to MDA will be compared with data collected in the 24 months following MDA.

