### Sample size

Sample size calculations were based on scabies prevalence in Western Province of Solomon Islands and the effect size measured in previous studies of ivermectin-based MDA for scabies.^6 17 21^ A standard Monte Carlo simulation method with 1000 repetitions was used to estimate the required sample size and number of villages to achieve statistical power of 80%.^49^ We assumed that scabies prevalence across villages would range from 10% to 30% (mean 20%, SD 5%) at baseline.^6^ The effect size measured in previous studies with two doses of ivermectin MDA was used to assume the prevalence of scabies 12 months after MDA will be between 3% and 9% (mean 6%, SD 2%) in the one-dose group and between 1% and 5% (mean 3%, SD 1%) in the two-dose group.^17 21^ We assumed an average village size of 250 people, with a range of 200 to 300.^50^ We considered a non-inferiority margin of 5% (prevalence of scabies at 12 months in the one-dose group minus prevalence at 12 months in the two-dose group) to be relevant from a public health perspective. Based on these assumptions, 20 villages, randomised equally, would be sufficient to achieve the required power.

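### The primary outcome is a nurse's clinical judgement in an open-label trial, and the article states neither masking of the follow-up examiners nor balancing of them across arms, so an arm-specific diagnostic shift at follow-up could bias the non-inferiority result in either direction

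*Protocol article*

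**What the plan says.** Study design states: "The RISE trial is a prospective, open-label comparison of one dose versus two doses of ivermectin-based MDA for the population-level control of scabies". Neither the text nor Table 1 makes an exception for outcome assessment.

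Under Outcome measures, "Examinations will be conducted by nurses from Western Province". On the diagnosis itself: "Categorisation will be based on the identification of typical scabies lesions, typical body distribution of lesions and presence of itch and/or positive contact history". Table 2 uses only B3, C1 and C2. All level A routes (microscopy, imaging device, dermoscopy) are marked as not used, as are burrows (B1) and genital lesions (B2). Clinical and suspected cases both count, and the note to the table adds the judgement on alternatives: "A diagnosis of clinical or suspected scabies should only be made if other differential diagnoses are considered less likely than scabies".

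The stated safeguards are the 2020 consensus criteria, one week of training, and a refresher: "Nurses will receive additional training prior to the follow-up surveys at 12 and 24 months". The Intervention section has ivermectin given by trained study staff. Whether any of them also examine is not stated.

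**The concern.** Treatment cannot be masked here, but the people who examine skin a year later largely can be. As described, the diagnosis depends on what a nurse regards as typical, on what residents report, and on weighing other causes. Each of these can move if the nurse knows the village's arm. Separately, an examiner team that worked mainly in one arm at follow-up would bring its own diagnostic threshold into the comparison, even with no expectation about the result. Training makes examiners more alike but does neither of the two things that would protect the comparison: withholding the arm, or spreading examiners evenly over the arms.

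What is at stake is the primary verdict. Expected prevalence after MDA is low and the margin is 5 percentage points, so a shift of a few diagnoses per village is not small beside the room that the design leaves.

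**Working it through.** **Inputs.** Sample size section: 12-month prevalence 6% (SD 2) with one dose and 3% (SD 1) with two; baseline 20% (SD 5); 250 people per village; margin 5 points; power 80%. Randomisation section: 10 villages per arm. Primary outcome section: village change from baseline, with the upper limit of a two-sided 95% CI compared with 5 points. The documents give no diagnostic accuracy or agreement by arm, so the shift b (observed minus true difference, one dose minus two doses) is an assumption, taken mainly as 1 point in either direction. One point is 0.01 × 250 = 2.5 diagnoses per village.

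**Formula.** With true difference δ, P(non-inferior) = Φ((5 − δ − b)/SE − 1.96), all in percentage points.

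**Step 1: the plan's own figure.** Take the SDs of 2 and 1 as total between-village SDs for the 12-month difference. SE = √((2² + 1²)/10) = 0.71. At δ = 3 and b = 0: Φ(2/0.707 − 1.96) = Φ(0.87) = 81%. This reproduces the stated 80%.

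**Step 2: two other standard errors.**
- 12-month difference with binomial sampling within villages: 6 × 94/250 = 2.26 and 3 × 97/250 = 1.16, so SE = √((4 + 2.26 + 1 + 1.16)/10) = 0.92.
- Change from baseline, with baseline and follow-up uncorrelated: SE = √((25 + 4 + 25 + 1)/10) = 2.35.

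**Step 3: insert a shift that arises only at follow-up.**

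| Comparison | SE | δ = 5, b = 0 | δ = 5, b = −1 | δ = 3, b = 0 | δ = 3, b = +1 |
|---|---|---|---|---|---|
| 12-month difference | 0.71 | 2.5% | 29% | 81% | 29% |
| 12-month difference with binomial sampling | 0.92 | 2.5% | 19% | 59% | 19% |
| Change score, uncorrelated baseline | 2.35 | 2.5% | 6% | 13% | 6% |

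Entries are the probability of declaring non-inferiority. For example, at δ = 5 and b = −1: Φ(1/0.707 − 1.96) = Φ(−0.55) = 29%, and Φ(1/2.345 − 1.96) = Φ(−1.53) = 6%. A half-point shift at δ = 5 gives 10.5% with SE 0.71.

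**Step 4: how far the change score can move.** The correlation between a village's baseline and follow-up prevalence is not given. With the same SDs, its upper bound of 1 gives SE = √(((5 − 2)² + (5 − 1)²)/10) = √2.5 = 1.58, and Φ(1/1.58 − 1.96) = Φ(−1.33) = 9%. So for any non-negative correlation the change-score figure lies between about 6% and 9%, and does not reach 29%.

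**Step 5: what subtracting baseline removes.** It removes a shift only if the same number of points is added at baseline and at 12 months in the same village. A shift prompted by knowledge of the arm at follow-up, or by a change of examiners at follow-up, stays in the change score in full.

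**The case against.** The strongest reply is that this is an article, silent on masking rather than saying that nurses knew the arm. Rosters, form layouts and village lists belong in a full protocol or manual, which is not shown. That stands: the absence of such details is not in itself a fault. What remains is what the article does state: an open-label trial without exception for assessors, a judgement-based outcome described at some length, and training and consensus criteria as the safeguards. If the examiners were in fact masked, the open-label description needs that qualification.

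Several stronger readings are tempting, and the documents do not support them:

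- **Baseline examiners knew the arm.** Randomisation follows village agreement and community awareness precedes MDA, but no section says that a village's arm was disclosed to examiners at baseline.
- **The examining nurses gave the drug, or teams worked arm by arm.** The article states neither.
- **Imperfect accuracy alone uses up the headroom.** Specificity of 98% in one-dose villages would add 0.02 × 94 = 1.88 points at 12 months, against 5 − 3 = 2 points of headroom. If it also applied at the 20% baseline it would add 0.02 × 80 = 1.60 points there, leaving only 0.28 in the change score. A constant sensitivity of 80% in one-dose villages even works against one dose. With a true 8% versus 2% at 12 months, the observed changes are 6.4 − 16 = −9.6 and 2 − 20 = −18, an observed difference of 8.4 against a true 6. Only a shift specific to follow-up carries the argument.
- **The bias favours non-inferiority.** Nurses who expect one dose to work less well could over-diagnose in one-dose villages and push the other way.

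It also counts for the plan that, with a true difference near 0, a 2-point shift against one dose still leaves P(non-inferior) at 99% (SE 0.71) or 90% (SE 0.92) on the 12-month difference.

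**Conclusion.** The point holds as a preventable risk of detection bias, not as evidence that bias occurred. If a 1-point arm-specific shift arose at follow-up and the true difference were at the margin, false non-inferiority would rise from 2.5% to about 6% on the change score with uncorrelated baseline, 19% on the 12-month difference with binomial sampling, and 29% on the setup that reproduces the plan's power. The change score is the analysis that the Primary outcome section describes, so the lowest of these figures is the one closest to the planned test; the 29% should not be quoted without its conditions.

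The result rests on an assumed shift size, on the plan's SDs read as total SDs, and on a normal critical value. A t critical value changes the 29% to about 27% in simulation. That the 80% power reproduces only for the 12-month difference is a separate matter.

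**What to change.** For the 12- and 24-month surveys, or whichever remain:

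1. Use the existing nurses, but assign none to a village where they took part in MDA.
2. Keep the arm off survey forms, REDCap screens and the village lists that examiners carry.
3. Rotate examiners or teams over equal numbers of one-dose and two-dose villages.
4. Record the examiner's ID with each examination.

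Trial status schedules these surveys for May to July 2020 and May to July 2021. If a survey has already been done, state who examined in which villages and whether they knew the arm.

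The cost is more travel planning, with no change to sample size or staffing. Concealment will be partial, because residents know how many doses they received and supply the itch and contact history themselves. For that reason, results for level B alone are at most supplementary: B3 needs both resident-reported items, which examiner masking does not protect.
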